## Results

3

Table 1 reflects the comparison of the biochemical and clinical variables and the lifestyle factors.

**Table 1 T1:** Comparison of the biochemical and clinical variables and the lifestyle factors.

	Study group (n = 50)	Control group (n = 50)	*P* value
Body weight			
Current smokers			
Glycosylated hemoglobin			
Fasting blood-glucose			
Energy intake			

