## Methods

2

This study will be conducted from May 2021 to August 2022 at Ningbo No.6 hospital. The experiment was granted through the Research Ethics Committee of Ningbo No.6 hospital (539D035) and recorded in research registry (researchregistry6348). The random numbers sequence is produced through the computer. The random numbers are hidden by the sequentially numbered opaque and sealed envelopes. The patients will be randomly assigned into the study group and control group and each group includes 50 patients. The duration of follow up is 2 months.

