### Inclusion and exclusion criteria

2.1

Patients will be included in this experiment if their ages are in the range of 18 to 65 years old and are diagnosed with T2DM with microalbuminuria and the patients who have signed the written informed consent. While the patients will be excluded if they have serious physical comorbidities and patients who are unwilling to offer the informed consent to take part in this experiment.

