### Smoking habits

2.5

All the smokers and their spouses in study group are invited to participate in the programs of standardized smoking cessation. The project is carried out in the form of group consultations with a maximum of 14 participants. Patients are educated about the benefits of quitting smoking, and the specific advice on how to cope with the temptation to start smoking again, containing the information on the substitutes of nicotine, which is provided free of charge.

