### Statistical analysis

2.7

Through utilizing the Microsoft Excel 2013, the data is recorded, and the analysis of all the data is carried out through utilizing IBM SPSS Statistics for Windows, version 20 (IBM Corp., Armonk, NY, USA). With the χ^2^-tests and independent *t* tests, the analysis for continuous variables and categorical variables are implemented respectively. All data are described with proper features, such as percentage, average and median. *P* value less than .05 indicates that there is statistical significance.

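### Current smoking is compared crudely among all 50 patients per group although only baseline smokers can quit, so the comparison is unbiased but needlessly imprecise

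*Protocol article*

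**What the plan says.** Four statements in the protocol article bear on this point.

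- **Results, Table 1.** This is the only table. It has five rows, one of which is "Current smokers". Its columns are headed by the two groups, each with n = 50, and a P value. There is no baseline column, change row or quit-rate row, and no time point.
- **Methods.** Allocation uses a computer-generated random sequence, and "each group includes 50 patients". No stratification is mentioned. On follow-up: "The duration of follow up is 2 months".
- **Smoking habits (2.5).** "All the smokers and their spouses in study group are invited to participate in the programs of standardized smoking cessation".
- **Statistical analysis (2.7).** Chi-square and independent t tests are the only tests named: "the analysis for continuous variables and categorical variables are implemented respectively". A P "value less than .05 indicates that there is statistical significance".

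Smoking is not an entry criterion. Besides consent and the absence of serious comorbidity, patients qualify if "their ages are in the range of 18 to 65 years old and are diagnosed with T2DM with microalbuminuria". Each group will therefore contain both smokers and non-smokers.

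**The concern.** The tabulated variable is smoking prevalence in everyone, while the programme can change smoking only in those who smoke at entry. The number of baseline smokers will differ between the groups by chance, and a crude comparison at follow-up carries that difference forward. The effect is also diluted: a given difference in quit rate moves the all-patient percentage only by that difference times the proportion who smoke.

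At stake is what the row can tell the reader about a component that has its own section in the intervention. If most of the spread in the estimate reflects who smoked at entry, neither the estimate nor its P value says much about quitting. The information needed to remove this noise must be collected anyway, because smokers have to be identified before they can be invited.

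**Working it through.** **Inputs from the article.** 50 patients per group; all-patient smoking row with a P value; unadjusted tests; significance at .05 (taken as two-sided).

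**Inputs assumed.** The article gives no smoking prevalence, quit rate or power calculation, so there is no figure of its own to reproduce. I take baseline smoking p = 30% (range 25% to 40%), quit rates of 30% in the study group and 5% in the control group, and no new smokers. I take the chi-square test for this row, since it is categorical. The sentence in 2.7, read literally, pairs the tests the other way round, but a t test on a yes/no variable would be crude in the same way.

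**Step 1, true difference at p = 30%.**
Study 0.30 × 0.70 = 0.210; control 0.30 × 0.95 = 0.285; difference = -7.5 points.

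**Step 2, crude standard error.**
√[(0.210 × 0.790 + 0.285 × 0.715)/50] = √(0.3697/50) = √0.007394 = 8.6 points.

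**Step 3, where that variance comes from.**
- Baseline smoking: p(1-p)/50 × (0.70² + 0.95²) = 0.0042 × 1.3925 = 0.005849.
- Quitting among smokers: p × (0.30 × 0.70 + 0.05 × 0.95)/50 = 0.30 × 0.2575/50 = 0.001545.
- The sum is 0.007394, as in step 2. The baseline share is 0.005849/0.007394 = 79%.

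**Step 4, standard error given baseline smoking.**
√0.001545 = 3.9 points by formula. In simulation, the difference in quit rate among baseline smokers, put on the all-patient scale, has a standard error of about 4.0. It is slightly larger because the number of smokers varies between trials.

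**Step 5, simulation (400,000 trials).** The crude test is the uncorrected chi-square on all patients. The alternative is Fisher's exact test among baseline smokers.

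| Baseline smokers | True difference (points) | SE crude / conditioned (points) | Wrong sign crude / conditioned | Power crude / Fisher |
|---|---|---|---|---|
| 25% | -6.25 | 8.1 / 3.7 | 18% / 3.6% | 12% / 23% |
| 30% | -7.5 | 8.6 / 4.0 | 16% / 2.6% | 14% / 31% |
| 40% | -10.0 | 9.4 / 4.6 | 12% / 1.3% | 18% / 46% |

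**Step 6, validity of the crude test.** With 5% quitting in both groups, its type I error is about 5%. In the scenarios of the table, a significant result in the wrong direction occurs in 0.1% to 0.3% of trials.

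**Step 7, other quit rates.** The standard deviation of the chance difference in baseline smoking is √[2p(1-p)/50]: 6.0, 8.0, 9.2, 9.8 and 10.0 points at 10%, 20%, 30%, 40% and 50% smokers. A 20-point difference in quit rate moves the all-patient percentage by 2, 4, 6, 8 and 10 points, never more than one standard deviation. A 40-point difference (10% against 50%) moves it by 12 to 20 points at 30% to 50% smokers, which does exceed it. Power of the crude test is still at most 56%.

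**The case against.** **The table may not be an outcome table.** It states no time point. If it shows baseline characteristics, the point does not apply. I read it as the outcome comparison because it is the only table and stands under Results, but this is an inference.

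**The article is condensed.** Adjustment or a quit-rate table may sit in a fuller document, and n = 50 in a column head is the group size, not expressly the denominator of the row. That is fair as a caution. The article does, however, fix a variable, a group comparison and a family of crude tests, and the point concerns those.

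**Randomisation protects the comparison.** This stands. A reader might infer that the row is biased or the test invalid. Neither follows: baseline imbalance is random, and the type I error is about 5%.

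**The wrong-sign rate sounds worse than it is.** This also stands. A reader might infer that the trial is likely to report, as a finding, fewer smokers in the group that quit less. The wrong sign concerns the point estimate. Inference in the plan is by P < .05, and a significant reversal is very rare. The likely result is a non-significant row.

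**The gain is limited.** At 30% smokers, the alternative rests on about 15 patients per group (0.30 × 50), and its power is about 31%. Smoking is one of five rows and is nowhere called primary, and the Discussion already concedes a small sample and short follow-up.

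**Conclusion.** The point holds as a matter of precision, not validity, and it is minor. Provided Table 1 shows outcomes, the crude smoking comparison spends most of its variance on who smoked at entry: 79% at 30% smokers, with a standard error about twice that of a comparison conditioned on baseline smoking. The harm is lost precision and a P value that says little about cessation.

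The size rests on assumed prevalence and quit rates, because the article gives none. It would therefore be too strong to say without qualification that imbalance overwhelms the effect. With a 40-point quit difference and at least 30% smokers, the effect is larger than one standard deviation of the imbalance.

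**What to change.** State in Table 1 that the values are at the end of follow-up. Then do one of the following for the smoking row:

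1. Keep all patients but adjust for baseline smoking status. A stratified (Mantel-Haenszel) risk difference is safer than logistic regression, which may fail to converge if no baseline non-smoker starts smoking.
2. Report non-smoking at the end of follow-up among baseline smokers: n/N per group, risk difference with 95% confidence interval, and Fisher's exact test because the expected counts are small.

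Label the row exploratory. The cost is one table row and one sentence. Baseline smoking status is already needed to invite smokers, and neither treatment nor sample size changes. The price of the second option is a small denominator. Neither option gives adequate power for smoking: about 23% to 46% for the second under the assumptions above, against 12% to 18% for the crude test.

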### Discussion

3.1

The number of T2DM patients is increasing rapidly, which has become a serious problem of health in the world. Obesity and sedentary lifestyle have been linked to an increase in the T2DM prevalence globally.^[13,14]^ For a long time, the educators of diabetic nursing have always regarded lifestyle education as the cornerstone of diabetes teaching, aiming to control the concentrations of blood glucose, help the patients improve their medical compliance, and slow down the progress of disease-related complications.^[15,16]^ The management of T2DM involves exercise, diet, and medication.^[17,18]^ However, adherence to these lifestyle measures has been sub-optimal in usual care for diabetes, leading to higher rates of mortality related to diabetes and poor glycemic control. In order to improve the prognosis of T2DM, we design the programs of structured lifestyle intervention. Considering that the sample size of our study is small and follow up is short, further high quality randomized controlled trial is required.

## Conclusion

4

Lifestyle education is effective in facilitating the control of T2DM and reducing microalbuminuria.
